## Abstract

**Background:**

Kidney transplant recipients remain at high cardiovascular risk despite improved graft and patient survival. Physical inactivity, weight gain, and suboptimal dietary habits are common after transplantation and may contribute to this burden.

**Methods:**

The KT-LIFESTYLE trial is a pragmatic, multicentre, prospective, open-label randomized controlled study designed to evaluate whether a structured lifestyle intervention can reduce cardiovascular risk in kidney transplant recipients. Participants will be randomized 1:1 to individualized exercise prescription plus tailored dietary counselling or standard lifestyle advice. The intervention combines multidisciplinary assessment, individualized exercise programming, motivational interviewing, and nutritional counselling integrated into routine transplant follow-up. The primary endpoint is the change in 10-year cardiovascular risk, assessed by the Framingham score over 36 months. Secondary outcomes include renal function estimated by Chronic Kidney Disease Epidemiology Collaboration (CKD-EPI) 2021 equation estimated glomerular filtration rate, body composition, inflammatory markers, gut microbiota composition, health-related quality of life, adherence to physical activity and dietary counselling, hospital admissions, major adverse cardiovascular events, and all-cause mortality.

**Conclusions:**

KT-LIFESTYLE aims to provide evidence on the effectiveness and feasibility of a long-term lifestyle intervention after kidney transplantation. The study may also clarify the mechanisms through which lifestyle modification influences cardiovascular risk, inflammation, body composition, and gut microbiota in this population.

Clinical trials registration number: NCT06806670

KEY LEARNING POINTS
**What was known:**
Both physical inactivity and unhealthy diet, known modifiable cardiovascular risk factors, are highly prevalent after kidney transplantation.Exercise training is safe and beneficial after kidney transplantation.Integrating exercise and tailored diet as part of daily life after kidney transplantation is highly recommended.
**This study adds:**
KT-LIFESTYLE will evaluate whether combined physical exercise and dietary counselling reduce cardiovascular risk in kidney transplant recipients.The study will provide evidence on the efficacy and adherence to ‘exercise and diet therapy’ correlated with lifestyle modification.Implementation outcomes will provide insights on successful strategies to promote sustained lifestyle intervention in this population.
**Potential impact:**
Results may contribute to guidelines on lifestyle interventions after kidney transplantation.Findings will inform the development of implementation strategies to reduce cardiovascular risk after kidney transplantation and to promote sustained lifestyle changes for improved long-term outcomes.This study could help clarify the impact of lifestyle on the gut microbiota and elucidate the relationship between the relative abundance of different bacterial taxa and cardiovascular risk.

## INTRODUCTION

Solid organ transplantation substantially improves survival and quality of life in patients with end-stage organ disease, allowing recovery of physical function and social and work reintegration. Despite these advances, kidney transplant recipients (KTRs) remain at markedly increased risk of cardiovascular disease, a leading cause of late morbidity and mortality in this population [1]. Observational studies consistently show that cardiovascular events occur more frequently in KTRs than in nontransplanted individuals, particularly in the presence of diabetes or established vascular disease [2]. Among modifiable risk factors, physical inactivity and unhealthy dietary habits are common after kidney transplantation and contribute to weight gain, metabolic complications, and worse graft and patient outcomes [3]. Current international recommendations, including World Health Organization (WHO) guidelines, advocate regular physical activity and healthy eating patterns for people with chronic diseases and transplant recipients [4]. Randomized and longitudinal studies in KTRs have shown that structured exercise programs, with or without dietary counselling, can improve aerobic capacity, body composition, metabolic profile, and health-related quality of life, although most trials are small, short-term, and rarely embedded in routine clinical pathways [3, 5]. Furthermore, longitudinal studies indicate that maintaining an active lifestyle is associated with better preservation of renal function over time, and that regular weekly training may counteract cardiovascular risk and slow renal function decline in kidney transplant patients [6]. In routine clinical practice, lifestyle counselling remains unstructured, heterogeneous across centres, and insufficiently standardized. Cardiovascular risk prediction tools may also help identify KTRs at higher risk of cardiovascular events. Several studies have applied the Framingham score in patients with chronic kidney disease (CKD) to predict cardiovascular events, although it may underestimate absolute risk in this population [7, 8]. Other studies suggest that, when combined with estimated glomerular filtration rate (eGFR), the Framingham score may help identify KTRs at increased risk of cardiovascular events and post-transplant renal dysfunction [9, 10]. In this context, the KT-LIFESTYLE trial aims to evaluate the effectiveness of a structured lifestyle intervention combining individualized exercise prescription and tailored dietary counselling in KTRs. We hypothesize that a 3-year intervention will reduce cardiovascular risk, assessed using the Framingham score, compared with standard care. The integrated modification of physical activity and dietary habits may therefore play a key role in cardiovascular risk reduction, and the novelty of this study lies in evaluating the potential of an integrated lifestyle intervention in reducing cardiovascular risk in KTRs.

## MATERIALS AND METHODS

### Study design and population

The KT-LIFESTYLE study is a pragmatic, multicentre, prospective, open-label, nonpharmacological randomized controlled trial. The primary endpoint is the between-group difference in change in the Framingham score over 36 months in KTRs receiving the lifestyle intervention versus standard of care. The Framingham score estimates the 10-year probability of a cardiovascular event using routinely collected clinical variables including sex, age, systolic blood pressure, smoking status, diabetes, high-density lipoprotein (HDL) cholesterol, and total cholesterol [11]. Secondary endpoints include renal function progression, assessed by eGFR calculated with the Chronic Kidney Disease Epidemiology Collaboration (CKD-EPI) 2021 formula [12], gut microbiota composition, body mass index (BMI), inflammatory markers [serum C-reactive protein (CRP), interleukin-6 (IL-6), and ferritin], metabolic assessment variation (including glucose and lipid profile) and adherence to physical activity counselling assessed by the International Physical Activity Questionnaire (IPAQ) [13], adherence to dietary counselling assessed by the Food Frequency Questionnaire (FFQ) [14], quality of life assessed by the Short Form-12 Health Survey (SF-12) [15], hospital admissions for significant clinical events, fatal and nonfatal cardiovascular events (major adverse cardiovascular events), and all-cause mortality. A maximal cardiopulmonary exercise test will be performed in a subgroup of 25 participants per group. No comparisons with the general population or other patient groups are planned. Annual interim analyses will assess data completeness, quality, and study conduct. Participants will be recruited from IRCCS AOU Bologna and AUSL Romagna Hospitals. The study population will include clinically, surgically, and functionally stable adult KTRs of both sexes followed in the outpatient setting. Participant enrolment will be based on the inclusion and exclusion criteria presented in Table 1. Written informed consent will be obtained from all participants, who will also complete baseline questionnaires on smoking status, alcohol consumption, pretransplant dialysis vintage, time since transplantation, cause of kidney failure, and comorbidities. Ethical approval (EM221-2025_138/2023/Sper/AOUBo) was obtained from the ethics committee. The study complies with the International Conference on Harmonization Good Clinical Practice guidelines and the Declaration of Helsinki.

### Randomization

Participants will be randomized 1:1 to the lifestyle intervention group, receiving individualized exercise prescription plus dietary counselling, or to the control group, receiving standard lifestyle advice. Randomization will be stratified by sex and age in 5-year intervals and performed using a secure electronic randomization system [16].

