#### Statistical analysis plan

All analyses will follow the intention-to-treat principle. Baseline characteristics will be summarized using mean ± SD or median (interquartile range) for continuous variables and counts and percentages for categorical variables. The distribution of variables will be examined before inferential analyses. The primary endpoint will be analysed using repeated-measures analysis of covariance (ANCOVA) , with group, time, and group-by-time interaction as fixed effects and age, time from transplantation, and dialysis duration as covariates. The same framework will be applied to secondary continuous outcomes, including eGFR, gut microbiota composition, BMI, inflammatory markers, and quality of life. Potential effect modifiers will include sex, pretransplant and current physical activity, and dietary characteristics. Mean between-group differences in change in Framingham score will be reported with 95% confidence intervals, and subgroup analyses will be performed by sex and age group. If model assumptions are not met, nonparametric analyses will be used. Discrete outcomes, including hospital admissions, cardiovascular events, and death, will be analysed using binomial or multinomial logistic regression. Safety will be summarized by the frequency and type of adverse events in each group. Data from all centres will be pooled for analysis.

**Table 1: tbl1:** Inclusion and exclusion criteria.

Male and female patients who are KTRs stabilized from a clinical standpoint (judgment by the reference transplant centre) Minimum age: 30 years completed Maximum age: 69 years completed Time from transplant: from 6 months (after achieving clinical stability) to 10 years Organ function: eGFR (CKD-EPI 2021 formula) ≥30 ml/min/1.73 m² Obtaining informed consent
Patients unable to follow the prescription Recent acute cardiovascular event (<2 months) Unstable angina Hyperkinetic/hypokinetic arrhythmias not controlled with therapy, and with signs of haemodynamic compromise Severe aortic stenosis Heart failure class NYHA III and IV, ejection fraction (EF) <40% Acute diseases limiting physical activity practice Severe hypertension (baseline blood pressure (BP) ≥200/110 mmHg) Neuro-musculoskeletal pathologies that may be aggravated by exercise Patients unwilling to change lifestyle Any form of substance abuse, psychiatric disorder, or condition that, according to the investigator, may complicate physician–patient communication Pregnant women

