Methodologically, the trial is pragmatic and multicentre, with concealed randomization through REDCap and stratification by age and sex. Individual randomization was deliberately chosen over cluster randomization primarily because the risk of cross-contamination in KT-LIFESTYLE is structurally limited. Furthermore, the ACT trial—the most directly comparable multicentre randomized controlled trial of exercise and diet in KTRs [3]—also employed individual randomization in a multicentre open-label design without reporting significant contamination issues. Finally, cluster randomization would have required a substantially larger sample size to account for the design effect, which was not feasible given the available patient population.

The embedding in routine follow-up, together with individualized exercise prescription, nutritional counselling, motivational interviewing, and scheduled contacts, enhances real-world relevance and may inform future guideline development. The following limitations should also be acknowledged. Open-label design may introduce performance and detection bias, particularly for behavioural and self-reported outcomes, although the primary endpoint is based on objective clinical variables.

In addition, adherence to exercise and diet is self-reported through the IPAQ and FFQ, which may be affected by recall and social desirability bias in the absence of objective measures such as accelerometry or dietary biomarkers. Concerning scalability, the study intervention is resource-intensive, requiring close coordination among nephrology, sports medicine, and nutrition teams, which may be a challenge in other settings.

KT-LIFESTYLE aims to address a major gap in the long-term management of KTRs by evaluating the efficacy in reducing cardiovascular risk through a lifestyle intervention based on physical activity and nutritional counselling.

This study also aims to evaluate feasibility, implementation with routine clinical practice, and scalability.

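### Randomisation is stratified by sex, but the primary model adjusts for age and not for sex, so its standard error may be slightly too wide

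*Protocol article*

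**What the plan says.** **Design.** The Randomization section says: "Randomization will be stratified by sex and age in 5-year intervals". The Discussion repeats it: "concealed randomization through REDCap and stratification by age and sex". Centre is named as a stratification factor in neither place.

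**Primary model.** The Statistical analysis plan section lists the terms of the repeated-measures ANCOVA: "group, time, and group-by-time interaction as fixed effects and age, time from transplantation, and dialysis duration as covariates". The same framework is then applied to the secondary continuous outcomes (eGFR, microbiota composition, BMI, inflammatory markers, quality of life).

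**Where sex does appear.** Sex has two other roles in that section: "Potential effect modifiers will include sex, pretransplant and current physical activity, and dietary characteristics", and "subgroup analyses will be performed by sex and age group". In Study design and population, sex is also listed among the inputs to the Framingham score.

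**Centre.** Study design and population says: "Participants will be recruited from IRCCS AOU Bologna and AUSL Romagna Hospitals". The only analysis statement is: "Data from all centres will be pooled for analysis".

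**The concern.** Stratifying by sex removes the chance difference in sex mix from the treatment comparison. An analysis that omits sex does not know this. It leaves the variation due to sex in the residual and reports a standard error that includes a component the design has already removed. Confidence intervals are then somewhat too wide and the test rejects too rarely. The usual remedy is to put the stratification factors in the model. Here one is in and the other is out.

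This is not detail left to a separate analysis plan, because the article itself fixes the covariate list. Naming sex as an effect modifier and subgroup factor does not repair the omission, since neither role adjusts the primary estimate. At stake is a small amount of precision in a design with no slack on the power it claims.

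**Working it through.** **Inputs from the Sample size calculation section:** difference 1 point, SD 8.1, correlation 0.95, α = 0.05 (taken as two-sided; not stated), power 80%, 99 per group completing, 10% dropout.

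**Step 1: the plan's own figure.** The baseline-adjusted residual variance is 8.1² × (1 − 0.95²) = 65.61 × 0.0975 = 6.397, so the SD is 2.529. Then n per arm = 2 × (1.960 + 0.842)² × 6.397 / 1² ≈ 100.4, rounded up to 101, or 202 in total against the stated 198. At 99 per arm the standard error is 2.529 × √(2/99) = 0.3595, and power is Φ(1/0.3595 − 1.96) = 79.4%. With change-score variance instead (SD 8.1 × √(2 × 0.05) = 2.561), n is 103 per arm and power at 99 is 78.4%. The ANCOVA variance is closer to the stated figure and matches the named method, so it is used below. The enrolment figures are exact: 198/0.90 = 220 and 220/0.80 = 275.

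**Step 2: effect of omitting sex.** Let R² be the share of residual variance that sex explains. The documents give no value, so 0 to 10% is assumed. With sex balanced by stratification:

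- correct SE = 0.3595 × √(1 − R²);
- SE reported without sex ≈ 0.3595, too wide by the factor 1/√(1 − R²);
- true type I error without sex = 2 × [1 − Φ(1.96/√(1 − R²))];
- power with sex = Φ(1/correct SE − 1.96).

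| R² (assumed) | SE too wide by | Type I error without sex | Power at 99 per arm with sex | n per arm for 80% with sex |
|---|---|---|---|---|
| 0% | 0% | 5.0% | 79.4% | 101 |
| 2% | 1.0% | 4.8% | 80.2% | 99 |
| 5% | 2.6% | 4.4% | 81.4% | 96 |
| 10% | 5.4% | 3.9% | 83.5% | 91 |

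**Step 3: simulation.** Sex-stratified randomisation, N = 198, 4,000 runs per setting. Further assumptions: 60% men, and sex explaining 10% of the baseline level.

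| R² | Model | True SD of estimate | Mean reported SE | Type I error | Power |
|---|---|---|---|---|---|
| 0% | ANCOVA | 0.356 | 0.359 | 5.0% | 78.8% |
| 0% | ANCOVA + sex | 0.356 | 0.360 | 5.0% | 78.8% |
| 5% | ANCOVA | 0.347 | 0.359 | 4.2% | 78.8% |
| 5% | ANCOVA + sex | 0.346 | 0.350 | 4.6% | 80.4% |
| 10% | ANCOVA | 0.342 | 0.358 | 3.9% | 80.2% |
| 10% | ANCOVA + sex | 0.340 | 0.341 | 4.8% | 83.0% |

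(The SD, SE and type I error columns are from runs with no effect, the power column from runs with a 1-point effect.) The true spread of the estimate barely changes, because stratification already balances sex; what changes is the reported standard error. Like for like, the power gain at R² = 10% is 83.0 − 80.2 = 2.8 points.

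**Step 4: which term is needed.** The endpoint is change over 36 months, and the listed terms include no baseline-score covariate. If baseline is therefore one of the repeated outcomes, write the score for person i at time t as (group and time terms) + γ·sexᵢ + error. The change is Y(36) − Y(0), and γ·sexᵢ cancels. In complete data a sex main effect then leaves the group-by-time contrast as it was. A simulation with the protocol's SD and correlation (20 runs per setting, assumed sex effects on change of 0 to 1.65 points) agreed: the main effect left the estimate unchanged and the SE the same to about 10⁻⁵, while sex-by-time cut the SE by about 0 to 4%. A main effect is enough only when post-baseline values are the outcome.

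**The case against.** The strongest reply is that the omission may not matter at all. With a correlation of 0.95, baseline adjustment or differencing absorbs most of what sex explains about the level of the score, and if sex does not predict change, nothing is lost. Any error is in the conservative direction, age is already adjusted for, and the residual shortfall from 80% power comes from how 198 was derived, not from leaving sex out. All of this stands and limits the size of the point. It does not remove the mismatch, which is plain in the text and almost free to mend.

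Three stronger readings are tempting and are not supported:

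- **Centre.** A reader might infer that pooling centres also contradicts the design. Centre was never a stratification factor, so omitting it does not depart from the randomisation, and pooling data does not rule out a centre term. The documents also do not say that the intervention teams differ by centre.
- **Recovered power.** A reader might infer that adding sex restores the claimed 80%. That depends on an R² the documents do not give: at 0% power stays at 79.4%. From the change-score variance (78.4%), even R² = 2% gives only 79.2%.
- **Effect modifiers.** IPAQ and FFQ also measure adherence, so a reader might infer that post-randomisation activity and diet will be used as modifiers. Set against pretransplant activity, current activity reads naturally as status at enrolment, and nothing says that follow-up values will be used. This is a point of wording.

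**Conclusion.** The point holds for sex and is minor to moderate. The analysis omits one of the two stratification factors from a covariate list that the article itself fixes, and the secondary continuous outcomes inherit the omission. The consequence is a reported standard error 0 to about 5% too wide and a type I error between 5.0% and 3.9%. There is no bias in the treatment estimate and no reason to change the sample size.

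These figures rest on a two-sided test, the baseline-adjusted variance from the protocol's SD and correlation, and an assumed sex R² of 0 to 10% of residual variance. The loss would be larger only if post-baseline levels were compared with no baseline adjustment (type I error about 3 to 4% if sex explains 10 to 20% of the baseline level, also assumed). The endpoint, defined as change, does not suggest that analysis.

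**What to change.** Add sex as a covariate to the primary model and to the secondary continuous models that share its framework, and keep age. Where baseline is one of the repeated outcomes, include sex-by-time as well. Sex can remain an effect modifier and subgroup factor in addition.

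Two smaller wording changes could go in at the same time. State that the activity and diet effect modifiers are values measured at baseline. Say whether a centre term will be included; it is an optional refinement for precision.

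The cost is a change of analysis wording, to be made before outcome data are analysed: one degree of freedom for sex, and one more per further time point if sex-by-time is included. Recruitment, data collection and the sample size are unaffected.

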### Study interventions

Outcome parameters will be assessed at predefined timepoints during routine clinical follow-up (Fig. 1).

**Figure 1: fig1:**
[figure not shown]
Schematic overview of the participant timeline and study outcomes measured per timepoint. T: timepoints (months); VO_2_max: maximum oxygen uptake; 30sCST: 30-s chair stand test.

In both groups, visits will be aligned with standard transplant care and limited to clinically stable patients without acute cardiological or surgical conditions. Routine evaluation includes blood tests, standard 12-lead electrocardiogram (ECG), cardiological assessment, and spirometry.

All enrolled participants will complete the SF-12 and IPAQ. Nutritional status will be assessed by anthropometry, bioelectrical impedance analysis (BIA), and dietary habits will be evaluated by the FFQ. Blood, urine, and faecal samples will be collected in the fasting state and stored for biobanking.

No changes to immunosuppressive therapy are planned; any adjustments will be made only by the transplant team according to routine practice.

### Lifestyle intervention

Once randomized, participants in the lifestyle intervention group will be referred to the sports medicine unit and then to the dietitian.

The physical activity intervention, through a multidisciplinary team composed of a sports physician and an exercise physiologist, will prescribe an individualized exercise program based on health status and physical fitness assessments [17–19]. Aerobic capacity will be assessed with a 1-km treadmill test for indirect estimation of VO₂max [20], while muscle strength will be measured by handgrip dynamometry [21], the 30-s sit-to-stand test [22], and submaximal strength tests of the upper-limb muscle groups using free weights [23, 24]. Exercise prescription will follow the 2020 WHO guidelines for individuals with chronic diseases, after excluding contraindications to exercise [25]. Adherence and progression will be monitored through scheduled telephone contacts every 2 months in the first year and every 3 months thereafter, using a motivational interviewing approach [26].

The nutritional intervention will promote healthy dietary habits to reduce cardiovascular risk; participants with a BMI <30 will receive nutritional counselling every 6 months, whereas those with a BMI ≥30 will follow an individualized weight-loss diet with reinforcement visits every 4 months in the first year and every 6 months thereafter [27] (Fig. 2).

